#### **6.10.4.2 Additional Analyses – Subgroup**

There are currently no plans for any subgroup analyses. If this changes, all subgroup analyses will need to be pre-specified in the SAP. An interaction term in the GEE model will most likely be used to estimate subgroup differences in efficacy.

#### **6.10.5 Analysis Population and Missing Data**

The primary analysis will be on the 'Intention-to-Treat' population, i.e. all those randomised and analysed according to the arm to which they were randomised.

It is likely that the proportion of missing data will be small. However, if the proportion of individuals with missing falls data is more than 5% a multiple imputation method (using baseline characteristics) will be used as the basis of a secondary sensitivity analysis.

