### **6.1.3.2 GP practices**

If a GP practice withdraws from the study before the care home has been recruited, then another GP practice will be recruited. If a GP practice withdraws, during the intervention period, it will not be replaced. All data collected up to that point will be kept and used according to the consent form and GP Agreement with the sponsor, both of which are signed by the GP.

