## 6.8 Sample Size

A sample size of 880 (440 in each arm) would detect a decrease in fall rate from 1.50 per individual over 6 months to 1.178 with 80% Statistical Power. This assumes that the number of clusters available will be 44, with a mean of 20 participants from each, a loss rate of no more than 20% and an ICC of 0.05 or less.

To balance any under recruitment with over recruitment (eventually balancing out over the whole study), we will recruit in all triads a mean of 20 participants. Any variation with these limits would need to be approved by TSG and or DMC.

These assumptions are based upon data from the CAREMED (29) study, which estimated a fall rate of 1.5 per individual over a 6 months period. The detectable difference (from 1.5 to 1.178) is a relative reduction of 21% which is half that detected within a UK based pharmacist led medication review service provided to care homes.

Data from the CAREMED (29) trial indicated a mortality rate of 33% and further loss to follow-up of 5% over 12 months. Thus, a reasonable estimate of total losses due to mortality or other reasons over 6-months would be 20%. However, we will use data, where possible, up to the point at which someone withdraws from the study (either voluntarily, or otherwise). Therefore, those lost to follow-up, for whatever reason, should contribute some information on falls rate to the study analysis.

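### The 5% trigger for the missing-falls sensitivity analysis pools both arms, so it can leave the check unrun when losses sit mainly in one arm

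*Protocol*

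**What the plan says.** Protocol 6.10.5 opens from the expectation that "It is likely that the proportion of missing data will be small". It then sets a numerical condition: "if the proportion of individuals with missing falls data is more than 5% a multiple imputation method", based on baseline characteristics, "will be used as the basis of a secondary sensitivity analysis". The section gives no separate figure for each arm or triad and does not define what makes a resident's falls data missing.

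Three other sections bear on what counts as missing:

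- **6.8 Sample Size** plans for 20% total losses over six months from death and other causes, but uses data up to withdrawal, so that "those lost to follow-up, for whatever reason, should contribute some information on falls rate to the study analysis".
- **6.6.3 Loss to Follow-up** keeps deaths out of its definition of loss.
- **6.1.3.2 GP practices** says "If a GP practice withdraws, during the intervention period, it will not be replaced", and that data gathered before the withdrawal are retained.

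Under 6.10.4.1 the primary model is a Poisson GEE that already includes baseline fall rate and prognostic variables.

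**The concern.** The trial compares two arms, so what matters about missing falls data is which arm they come from, why they are missing, and how the unobserved fall rates differ from the observed ones. A single pooled percentage carries none of this. It can stay at or below 5% while one arm has lost nearly a tenth of its residents, and it can exceed 5% when the losses are even.

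Clustering makes uneven loss plausible. The randomised unit is a triad averaging 20 residents (6.7), and a practice that leaves during the intervention is not replaced, so losses can come in blocks.

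At stake is whether the report contains a robustness check on the primary result when it is most wanted. This is a rule that the protocol fixes, not a detail it leaves open, and it is the only missing-falls analysis the protocol states.

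**Working it through.** **Inputs.** 880 residents, 440 per arm, 44 triads averaging 20, 20% loss, ICC 0.05, and a "decrease in fall rate from 1.50 per individual over 6 months to 1.178 with 80% Statistical Power" (all 6.8); trigger above 5% of individuals (6.10.5); significance level 5% (6.10.4.1), taken as two-sided.

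**1. The plan's own sample size.**

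- Per arm before clustering: (1.96 + 0.842)² × (1.50 + 1.178) / (1.50 − 1.178)² = 202.7.
- Cluster size after 20% loss is 16, so the design effect is 1 + 15 × 0.05 = 1.75.
- 202.7 × 1.75 = 354.8; divided by 0.80 this is 443.5 per arm, or 887 in total, within 1% of 880.
- With cluster size 20 (design effect 1.95) and the same inflation the total is 988, which does not match.

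The 880 is therefore matched by a calculation in which the lost 20% contribute nothing, although the text of 6.8 expects them to contribute partial data.

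**2. The trigger.** 5% of 880 is 44, and the rule says more than 5%, so at least 45 residents must be missing.

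| Residents without falls data | Overall | Arm with more missing | Triggered? |
|---|---|---|---|
| 40 in one arm (two triads of 20) | 40/880 = 4.5% | 40/440 = 9.1% | No |
| 44 in one arm | 44/880 = 5.0% | 44/440 = 10.0% | No |
| 45 split 23 and 22 | 45/880 = 5.1% | 23/440 = 5.2% | Yes |
| 40 in one arm plus 5 others | 45/880 = 5.1% | 9.1% to 10.2% | Yes |
| Two triads of 23 in one arm | 46/880 = 5.2% | 46/440 = 10.5% | Yes |
| Three triads of 20 in one arm | 60/880 = 6.8% | 60/440 = 13.6% | Yes |
| All planned 20% losses | 176/880 = 20% | 20% if even | Yes |

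The untriggered cases require almost complete data elsewhere. After two triads of 20 are lost, 5 more missing among the other 840 (0.6%) fire the rule.

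**3. What an arm-specific check would examine (illustration on assumed values).** Suppose 10% of the intervention arm only is unobserved, with a true fall rate k times the observed one. The observed rate is then 1.178 / (0.9 + 0.1k), against 1.50 in control; the true rate ratio is 1.178/1.50 = 0.785.

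- k = 1.5: 1.122/1.50 = 0.748
- k = 2: 1.071/1.50 = 0.714
- k = 3: 0.982/1.50 = 0.654

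With 5% missing in each arm and the same k in both, the ratio stays at 0.785. With 5% in each arm, k = 2 in intervention and k = 1 in control, it is (1.178/1.05)/1.50 = 0.748. Equal proportions do not guarantee an unbiased comparison. With k = 1, unequal proportions cause no bias. The protocol gives no value for k.

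**The case against.** Four stronger readings are tempting, and the documents do not support them.

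- **That one-arm losses of this size never fire the trigger.** One to five further missing residents fire it, as do slightly larger triads. If the planned 20% losses count as missing, it fires regardless.
- **That a withdrawn triad has no falls data.** Section 6.1.3.2 retains what was collected before a practice leaves, 6.1.3.1 continues data collection after a PIP leaves, and 6.1.3.3 seeks another home if one leaves early. Falls are also collected at three months (6.5). A triad has no follow-up falls data only if it leaves before that collection and nothing later is obtained.
- **That the rule reduces power or inflates type I error.** The imputation is only a secondary sensitivity analysis, so the primary estimate and its test are identical whether or not it is run. Any such figures would describe an assumed bias in the primary estimate, which this rule neither creates nor removes.
- **That imbalance between arms is itself the bias.** Step 3 shows it is neither necessary nor sufficient.

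It can also be said that missing-data detail belongs in the SAP, which is not among the documents and may refine the rule; 6.10.3 and 6.11.1.2 already provide for recording non-retention and monitoring withdrawal rates. That stands for definitions and reporting tables. It does not remove the threshold that the protocol itself states.

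**Conclusion.** The point holds as a modest one. The 6.10.5 trigger looks at one pooled proportion and ignores where losses fall: 9.1% or 10% of one arm can be missing without firing it, provided data elsewhere are almost complete, while 45 missing residents spread evenly do fire it.

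The undefined term makes this harder to judge. If the planned 20% losses count as missing, the trigger is redundant and the expectation of little missing data is wrong. If partial follow-up counts as observed, the trigger may stay silent despite substantial unobserved time. Sections 6.8, 6.6.3 and 6.10.5 together do not settle which applies.

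The consequence is limited to a robustness check that may not be run. The rate ratios of 0.748 to 0.654 against 0.785 rest on assumed values of k and on 10% of one arm being wholly unobserved. They show what such a check would explore and do not forecast this trial's bias.

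Even when triggered, the planned imputation would add little, because it draws on baseline characteristics and the primary model already adjusts for baseline fall rate and prognostic variables. A departure specific to one arm would go largely untested.

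**What to change.** In 6.10.5, and in the SAP to match:

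1. Remove the pooled 5% condition and run the missing-falls sensitivity analysis whatever the proportion.
2. Report missing and partial falls follow-up by arm and by triad, stating how death, transfer and withdrawal are classed.
3. Add an arm-specific analysis that varies the fall rate assumed for unobserved follow-up in one arm at a time, and show how far it must move before the conclusion changes. This is the most useful of the three.

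The cost is about one sentence of protocol text and one more sensitivity table. No extra data or residents are needed, and the primary analysis is unchanged. It is best settled before outcome data are seen.

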It is possible that the introduction of the PIP could have implications for GP time e.g. GP visits to the care home could be more or less frequent/longer or shorter with a PIP, a medication review/repeat prescriptions may also require less or more GP input. The same may be true for care home staff as medication administration/management in the home may change. It is however unclear that such activities will be recorded in the primary medical notes/care home records. Therefore, in an attempt to try and capture this information, at study registration, GPs will be asked at recruitment to provide information about current activity (frequency, associated time, etc.) in relation to medication reviews, repeat prescriptions and care home visits. Additionally, in staff interviews/focus groups at the end of the study (intervention arm only) GPs will be asked to consider what effect the PIP has

had on such activities i.e. to try and identify whether there are perceptions of associated cost savings (e.g. fewer medication reviews) or cost increases (e.g. more tests/referrals), and the extent of these (if applicable). A similar approach will be taken with care home staff, where this will include asking whether they have done anything in addition to usual practice e.g. training, since the introduction of the PIP. Additionally, we will ask the number of pharmaceutical advisory visits the home has had; this may be, for example, if a Health Board (HB) or CCG pharmacist has visited the care home.

Estimates of resource use will be based on methods used by the applicants previously [9] and will subsequently be attached to items of resource-use in order to estimate the mean overall cost in each study-arm. This will enable the mean incremental cost of the PIP intervention to be estimated.

Quality of life will be assessed via the EQ-5D-5L[6]. For all participants, the proxy version will be completed by a member of the home care staff, such as a nurse or health care assistant who knows the resident; where a participant has capacity a self report version will also be completed. Use of the EQ-5D enables QALY (Quality Adjusted Life Year) scores to be estimated[7]. This will enable the mean difference in QALY scores between usual care (control) and the PIP intervention to be estimated (incremental effect).

The above analyses will enable both the incremental cost and incremental effect associated with the PIP intervention to be estimated. If one option is found to be both less expensive and more effective, then that option would be said to dominate the other and be estimated to be cost-effective. Alternatively, the mean incremental cost effectiveness ratio (ICER) [12] will be estimated, where if this falls below a threshold value of e.g. £20,000 per QALY [7] then that would suggest the more expensive technology was cost-effective. The associated level of uncertainty will also be characterised by estimating cost-effectiveness acceptability curves. Sensitivity analysis will also be undertaken to assess the robustness of conclusions to changes in key assumptions. All analysis will be conducted on an intention-to-treat basis.

## 6.11 Data Monitoring

### 6.11.1 Data Monitoring Committee

A Data Monitoring Committee has been established to monitor the trial. Details of membership, relationship with other committees' decision making processes and the timing and frequency of interim analyses are described in detail in the CHIPPS trial DMC Terms of Reference (ToR).

#### 6.11.1.2 Interim Analyses

No efficacy interim analyses are planned. Analysis of recruitment rates, withdrawal rates etc. will be monitored as part of the internal pilot and full trial.

#### 6.11.2 Data Monitoring for Harm

The DMC will be provided with safety data for each treatment arm. This will include frequency of serious adverse events (hospital admissions and deaths,) in both arms and those adverse events which are defined as sudden, unexpected, serious adverse events (likely to be related to the study intervention) in the treatment arm. The committee will advise on the continuation or early stoppage of the trial in the unlikely event that there are concerns over harm to participants.

### 6.11.2.1 Safety reporting of Serious Adverse Events

The principles of ICH GCP require that investigators and sponsors follow specific procedures when notifying and reporting adverse events or adverse reactions in clinical trials. The processes for the recording of SUSARs, SAEs and AEs and near misses in PIP documentation, GP and care home records, notification to NCTU, CI review, expedited and periodic reporting to REC will be documented in the study specific Safety Management Plan.

For the purposes of this trial, SAEs are defined as in patient hospitalisation and death. The expedited i.e. immediate reporting is required if they are:

- **related** to the study (i.e. they resulted from the intervention) and
- **unexpected**

- referred to hereafter as SUSARs.

A mixture of prospective and retrospective SUSAR notification will be used.

**Prospective:** GPs will be asked to report SUSARs immediately via a SUSAR Form to a dedicated NCTU safety email address (See section 6.11.2.1.2). GPs should report any SUSARs related to the PIP intervention from the beginning of the intervention until 30 days after the intervention.

**Retrospective:** A systematic retrospective collection of SAEs will be conducted in both intervention and control practices, whereby the NCTU Trial Manager will contact every participating care home once a month and ask about any SAEs.

Deaths and hospitalisations in both arms will also be reported to REC via the annual report.

#### 6.11.2.1.1 Causality

The causality assessment of the SAE should be given by the GP. If the GP identifies a positive causality (i.e. the SAE is linked to the PIP intervention and is therefore a SUSAR) then this is signed off by the CI. The GP must assess the causality of all serious adverse events in relation to the PIP intervention using the definitions in the table below. If the event is classified as 'serious' and assessed as being related to the PIP intervention then an SUSAR form must be completed and NCTU notified within 24 hours (see 6.11.2.1.2. below)

**Table 1: SAE Causality Definitions**

| Event type | Causality assessment | Description                                                                             |
|------------|----------------------|-----------------------------------------------------------------------------------------|
| SAE        | Unrelated            | There is no evidence or rationale for any causal relationship.                          |
| SUSAR      | Likely to be related | There is evidence, and a rationale, to suggest a causal relationship and other possible |

|  |  |                                        |
|--|--|----------------------------------------|
|  |  | contributing factors can be ruled out. |
|--|--|----------------------------------------|

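### The SAE causality table has no class for a plausibly related death or admission with competing causes, and separately SUSAR is defined inconsistently

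*Protocol*

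**What the plan says.** All references are to the Protocol.

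- **What counts as serious (6.11.2.1).** "For the purposes of this trial, SAEs are defined as in patient hospitalisation and death". Causality plays no part in this definition.
- **What is expedited (6.11.2.1).** "The expedited i.e. immediate reporting is required if they are" related "to the study (i.e. they resulted from the intervention) and" also unexpected. Events meeting both conditions are called SUSARs.
- **Who judges causality, and how (6.11.2.1.1).** The GP must do so for all SAEs, using the definitions in Table 1. A positive judgement means that "the SAE is linked to the PIP intervention and is therefore a SUSAR", subject to sign-off by the chief investigator. The section adds: "If the event is classified as 'serious' and assessed as being related to the PIP intervention then an SUSAR form must be completed", with notification of the trials unit within 24 hours.
- **Table 1 (SAE Causality Definitions).** An SAE is unrelated when "There is no evidence or rationale for any causal relationship". It is a SUSAR, likely to be related, when "There is evidence, and a rationale, to suggest a causal relationship and other possible" "contributing factors can be ruled out". There is no third row.
- **What the DMC sees (6.11.2).** It sees SAE frequencies in both arms and, for the treatment arm, a category described as sudden, unexpected, serious and likely to be related. The abbreviations list (section 3) expands the first letter of SUSAR as suspected, not sudden.

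**The concern.** A causality scale that assessors are required to use should have a place for every event. This one sets a very low bar on one side (nothing at all to suggest a link) and a very high bar on the other (evidence, rationale and exclusion of other contributors), with nothing between them.

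The missing middle matters in this trial. Section 5.1 describes residents as generally frail, with multiple morbidities and many regular medicines. The intervention in 6.4 includes deprescribing, changing doses and starting medicines. An admission after a medicine change will often have a rationale, while another contributor can seldom be ruled out.

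Two things depend on the class chosen: the 24-hour form, and the DMC's listing of related events in the treatment arm. If GPs have no class for intermediate events, both may be under-populated or filled differently from one practice to the next. The inconsistent SUSAR definition adds a separate source of variation, because two GPs who each follow the Protocol could report a related but expected admission differently.

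**Working it through.** The Protocol gives no figure to reproduce on this point. The check is a comparison of definitions.

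**1. Is Table 1 exhaustive?** Its wording uses three yes/no elements: evidence of a link (E), a rationale for a link (R), and other contributing factors ruled out (O). That gives 2 × 2 × 2 = 8 combinations.

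| E | R | O | Table 1 class |
|---|---|---|---|
| no | no | no | Unrelated |
| no | no | yes | Unrelated |
| no | yes | no | none |
| no | yes | yes | none |
| yes | no | no | none |
| yes | no | yes | none |
| yes | yes | no | none |
| yes | yes | yes | Likely to be related (SUSAR) |

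Classified: 2 + 1 = 3. Unclassified: 8 − 3 = 5.

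This reads the unrelated row as requiring that both evidence and rationale be absent, which is its natural sense. Suppose instead that the absence of either one were enough. The unrelated row would then take six combinations and the related row one, leaving 8 − 7 = 1. That one is the case that matters most: evidence and rationale present, other factors not ruled out. It has no class on either reading.

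**2. Where does an unclassified death or admission go?**

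| Route | Section | Reached? |
|---|---|---|
| Monthly SAE collection, both arms | 6.11.2.1 | Yes |
| Annual report to the ethics committee | 6.11.2.1 | Yes |
| DMC review of SAE frequencies | 6.11.2, 6.11.2.1.3 | Yes |
| Immediate report of a concern by staff involved in care | 6.11.2.1.2 | Possible, if someone raises it |
| SUSAR form within 24 hours | 6.11.2.1.1, 6.11.2.1.2 | No defined route |
| DMC listing of related events, treatment arm | 6.11.2 | No defined route |

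**3. Is SUSAR defined once?** Take an SAE that is related to the intervention.

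| Source | Related and unexpected | Related but expected |
|---|---|---|
| 6.11.2.1 | SUSAR | not a SUSAR |
| 6.11.2.1.1 | SUSAR | SUSAR |
| Table 1 | SUSAR | SUSAR |
| 6.11.2 | listed, if also sudden | not listed |
| Section 3 (abbreviations) | SUSAR, on suspicion | not a SUSAR |

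The right-hand column contradicts itself. The left-hand column agrees on expectedness, but 6.11.2 adds suddenness, and the abbreviation's threshold of suspicion is well below Table 1's requirement to exclude other factors.

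**4. Are the two faults linked?** No. Step 1 concerns the threshold for relatedness, and step 3 concerns expectedness. Dropping expectedness, as 6.11.2.1.1 and Table 1 do, makes more related events reportable. It neither creates nor closes the gap in step 1.

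**The case against.** The strongest reply is that little is lost from view. Every death and inpatient admission is an SAE whatever its cause, is collected monthly in both arms, goes to the ethics committee each year and reaches the DMC by arm. The DMC also reviews unblinded data by practice and by home. Staff can raise any event that worries them at once, and geriatricians review a 20% sample of care plans (6.11.3.2). The by-arm comparison of deaths and admissions needs no causality judgement. All of this stands, and it limits the point. It does not close the gap: counts carry no causality assessment, and no rule says how a raised concern is to be classified.

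A second reply is that 6.11.2.1.1 speaks of an event being linked or related, so a GP who believes in a link has text telling them to submit the form. That is fair, and no passage directs non-reporting. But the same section ties the judgement to Table 1, so the instruction is at best ambiguous.

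A third is that 6.11.2.1 leaves processes to a Safety Management Plan, and Appendix 5 also lists SAE guidance. These are not available here and may help GPs with intermediate cases. They would not remove a conflict in the Protocol's own mandatory definitions.

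A reader might infer more than the text supports:

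- **That such an event is not reportable at all.** It is, by the routine routes above.
- **That the system would return no related events whatever happened.** The Protocol sets no default for unclassified events, and the concern route has no causality threshold.
- **That the internal-pilot safety criterion rests on Table 1.** Section 6.5 refers to neither Table 1 nor SUSARs, and 6.11.2.1.2 and 6.11.2.1.3 name SUSARs and safety concerns as separate things.
- **That expected mortality sizes the problem.** The 33% yearly mortality in 6.8 implies roughly 73 (440 × 0.165) to 80 (440 × (1 − √0.67)) deaths in one arm over six months. Those are deaths from all causes and say nothing about how many would be misclassified.

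**Conclusion.** Two separate faults hold, and both are wrong as written.

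First, Table 1 is mandatory but not exhaustive. It covers three of eight combinations of its own elements. The case left out on any reading is a plausible link with competing causes, and that event has no defined path to 24-hour reporting or to the DMC's related-event listing.

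Second, SUSAR carries conflicting definitions, so a related but expected event is expedited under one section and not under another.

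The likely effect is under-reporting or inconsistent reporting of related events. Overall SAE counts, the falls outcome and its analysis are not affected. The frequency cannot be estimated from the documents. That the gap would be common is a judgement from the described frailty and multimorbidity, not a calculation. The conclusion assumes that GPs apply Table 1 literally and that the unseen safety documents do not override it.

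**What to change.** - Make the causality classes cover every case. Either add a class for possibly related events (a reasonable possibility, other contributors not excluded), or remove the requirement that other factors be ruled out and redraw the two classes so that they meet. Either closes the gap.
- State which classes trigger the 24-hour form and which enter the DMC's listing.
- Record expectedness as its own item, separate from causality.
- Reconcile section 3, 6.11.2, 6.11.2.1, 6.11.2.1.1 and Table 1 to one SUSAR definition, including whether the first letter means sudden or suspected.

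The cost is rewording the Protocol, the SAE form and the Safety Management Plan, plus some additional reports to review. The sample size, randomisation and outcome analysis do not change.
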